### Surgery and the deep brain stimulation system

The DBS system to be used in this study is the Activa PC pulse generator, a dual-channel programmable device. The programmable stimulation settings are stored in the device and are a specific combination of pulse width, rate, and amplitude settings. The entire system, manufactured by Medtronic, is comprised of implanted and nonimplanted components. The components used in this protocol are as follows:The implantable pulse generator (one/subject) (Medtronic, Activa PC model 37601).The intracranial leads (two/subject) (Medtronic, model 3387). The leads contain the electrodes that deliver the stimulation.The lead extension wires (two/subject) (Medtronic, model 37085). These make the connection between the leads and the pulse generator.Stimloc burrhole cover. This component is used to secure the lead to the skull and cover the burrhole.The N’Vision clinician programmer (Medtronic, model 8840). This controls the pulse being generated.

In this trial, we will use the device as it comes from the manufacturer. The surgical implantation of the device follows the same technique used for movement disorder surgeries. The stimulation parameters that will be used in this protocol are commonly used in movement disorder and therefore the energy demand on the device will be the same as typically used in movement disorders.Following the standard surgical procedure for DBS system implantation, the patients will undergo the placement of a Leksell (Elekta, Atlanta, GA, USA) stereotactic frame. The electrode trajectory will be planned using stereotactic software (BrainLab, Munich, Germany). We will follow a traditional transfrontal trajectory (Figure 1). The transfrontal trajectory to the amygdala is a well-documented procedure traditionally used for stereotactic amygdalotomy. We will implant the DBS electrodes bilaterally in the BLn. A curvilinear incision will be made bilaterally 3 cm lateral to midline and 1 cm in front of the coronal suture. A burr hole will be placed bilaterally with a high-speed drill for placement of a Stimloc device (Medtronic, Minneapolis, MN, USA) to hold the electrode in place. Once the Stimloc is attached with the two self-tapping screws, the dura will be opened. The dura will be coagulated back and the cortex exposed, coagulated, and pierced. The electrode 3387 (Medtronic, Minneapolis, MN, USA) will then be introduced down the cannula. All the contacts of the electrode will then be stimulated at incremental voltages up to 7 volts to confirm the absence of immediate side effects by the study neurophysiologist (SK) while the patient is awake and is being examined by the study psychiatrist (RK, HS) and neurosurgeon ([name]). The left electrode will be inserted and tested first for side-effects, and then, the right electrode will be inserted and tested. In the absence of serious adverse effects, the stimulators will be turned off and the electrodes will then be tunneled under the skin down to the upper chest area. They will be connected to a dual-channel pulse generator Activa PC (Medtronic, Minneapolis, USA).

After surgery, patients will be kept in the hospital for approximately 3 days to ensure postoperative safety/stability. Then patients will return to the clinic for weekly safety evaluations for the first five months. Stimulators will be kept off in all patients for the first four weeks. Then, once the EEG telemetry session described below is complete, patients will be assigned randomly, in a double-blind fashion (only the study neurophysiologist will know) to have stimulation initiated at that 4-week postoperative time point, or after an additional 2 months (that is, 3 months postoperatively).

### Electroencephalogram telemetry session and deep brain stimulation initiation

At week 3 or 4, before initiation of experimental stimulation, each subject will be admitted to the Neurology EEG Telemetry Unit under the direction of JC for testing of stimulus parameters with real-time EEG to rule out after-discharges that would place patients at high risk of seizures, changes in vital signs that would place patients at risk of adverse health outcomes, changes in cardiac rhythm on electrocardiogram (ECG), or changes in behavior that would pose significant safety risk if they were to occur at home in an unsupervised setting. During the telemetry session, the electrodes will be initially stimulated at 2.5 V, 120-μsec pulse width, and 160-Hz frequency. The amplitude will then be progressively increased slowly to a maximum of 7 V. The pulse width will then be increased to a maximum of 210 μsec. Finally, the frequency will be increased to a maximum of 200 Hz. Side effects will be specifically noted throughout the session. If a serious side effect is noted, the last parameter changed will be kept at a maximum of 60% of the threshold value during subsequent long-term stimulation, and the other parameters will not be increased. For instance, if an after-discharge is noted for the first time at 5 V, the patient will continue in the study following our protocol, but the stimulation parameters will be kept below 3 V.

After the telemetry session, the DBS treatment will be initiated in a staggered fashion. Following the operation, patients will be randomized into two groups of three subjects. The first group will undergo therapeutic stimulation beginning 30 days postoperatively. The second group will start the stimulation at 90 days postoperatively. All the patients will undergo programming sessions of the same duration whether actual stimulation is provided or not, and the patients, the neurosurgeon, and the psychiatrists performing the evaluations will be kept blind to the treatment assignment.

We will also perform monthly EEGs for early detection of newly developed epileptiform discharges after initiation of stimulation. Subjects with newly developed epileptiform discharges will be terminated from the study and managed clinically.

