In its current application, DBS electrical current is modulated by frequency, pulse width, and amplitude. These parameters can be modified postoperatively with an external programmer. Reversibility is an obvious benefit of this treatment over resection or a destruction procedure. While the exact mechanism of action is not yet fully understood, it is relevant that the brain is a voltage sensitive organ, composed of numerous ion channels with different voltage sensitivity and activation ranges. The neurophysiological responses from an electrical stimulation can be determined from the voltage changes at a specific tissue site and the subsequent activations of ion channels. Variations of how the stimulating current is delivered, such as by changing the stimulation pulse width, the amplitude and the frequency, would result in differences in the extent of tissues that could reach the target voltage. The stimulated tissues could be modeled as a sphere with the tip of the stimulation electrode at the center. The stimulation effect, or the induced voltage change, is impedance dependent and tapers down, moving further away from the center of stimulation. After a tissue is stimulated, the activation of various ion channels subsequently plays an active role in determining the final neurophysiological effects[86]. Clinically, we can approximate the stimulated effect as pulse width determines the surface area of neural tissue covered by the stimulation, amplitude determines the strength of the effect, and frequency determines activation or inhibition. High frequency stimulation blocks the activity of the neural structure and clinically mimics the effects of a lesion[87–89], although electrophysiological monitoring has shown that neural fibers can be activated even with high-frequency DBS[87]. A current model holds that DBS adds a significant amount of interference to the final output signal from the nucleus, therefore rendering the output signal meaningless. This process is referred to as ‘frequency jamming’. Several other hypotheses of DBS mechanisms have been put forward, and it is likely that mechanisms of action differ in different conditions and targets. In each of the psychiatric conditions in which it has been studied, DBS targets have been chosen based on functional neuroimaging findings of abnormal brain circuitry. In both depression[73] and OCD[90], high-frequency DBS targeted to an area of hyperactivity normalizes metabolism in interconnected brain regions. Similarly, in Alzheimer’s Disease, functional connectivity with hippocampus and cerebral cortex increased after 1 year of DBS in the nucleus basalis[91].

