**Transfrontal trajectory for deep brain stimulation of the basolateral amygdala.**

Electrical stimulation of the amygdala in humans has also been performed in patients undergoing depth electrodes for epilepsy monitoring[143–145]. The amplitude delivered to the tissue was up to 10 mA, several fold higher than the recommended DBS parameters. The smaller diameter of those electrodes compared to the current DBS implant also means that the charge density delivered was several times higher than the maximum allowed by the Medtronic Activa system we will use in this study. In addition, the frequency was kept low: between 5 to 10 Hz, approximately 10 to 20 times lower than currently used for movement disorders, and 20 to 30 times lower than planned in this investigation. These settings were meant to generate seizures or other symptoms that would be related to the amygdala. The authors were intrigued that very few patients reported significant anger despite the elevated settings of stimulation. In addition, few convulsions were noted despite the high-amplitude and the fact that the patients were suffering from medically refractory temporal lobe epilepsy[143]. In our protocol, the amygdala tissue disruption and the electrical charge density are both several folds (that is, 10 to 20 times) smaller than listed in previous reports concerning amygdala neurosurgery. Therefore, we expect our safety profile to be considerably better. In addition, we are benefiting from the advances in surgical and imaging techniques since those reports were published.

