### Deep brain stimulation programming

Following the initiation of stimulation, stimulation parameters will be adjusted based upon the patient’s CAPS scores and other aspects of response to DBS therapy. Only one parameter can be changed at a study visit. The neurophysiologist performing the programming will be provided with the CAPS score and will adjust the parameters, based on the following protocol (sham adjustments will be made during the first 2 months in subjects who are randomized to initiation of stimulation at 90 days post-implantation):amplitude increase,amplitude increase,pulse width increase, thenfrequency change.

Any further programming changes will be based on the patient’s CAPS scores, the response to DBS therapy, and the clinical judgment of the study team. In order to prevent any damage to the neural tissue, we will keep the charge-density threshold below 30 microcoulombs/cm^2^/phase. The programming device automatically provides measurement warning if this threshold is exceeded. Following every change, the patients will be monitored for any side effects. The parameters will be reverted if the subject experiences any sustained side effects.

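### The 60% back-off rule does not work for the frequency step of telemetry: every possible limit falls outside the frequencies tested under EEG

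*Protocol article*

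**What the plan says.** The telemetry section sets the starting point: "the electrodes will be initially stimulated at 2.5 V, 120-μsec pulse width, and 160-Hz frequency". It then gives the order of escalation. "The amplitude will then be progressively increased slowly to a maximum of 7 V"; pulse width follows, to at most 210 μsec; and "Finally, the frequency will be increased to a maximum of 200 Hz". Nothing says that amplitude or pulse width is brought back down before the next parameter is raised.

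If a serious side effect occurs, "the last parameter changed will be kept at a maximum of 60% of the threshold value during subsequent long-term stimulation". On the two remaining settings the rule adds only this: "and the other parameters will not be increased". The single illustration is an after-discharge first seen at 5 V, after which stimulation stays below 3 V.

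Other sections bear on how the rule operates:
- Deep brain stimulation programming adjusts one parameter per visit: two amplitude increases, a pulse-width increase, then a frequency change. It also sets a charge-density limit of 30 microcoulombs/cm²/phase. It does not mention subjects limited at telemetry.
- Risk reduction measures (Neuromodulation) starts long-term stimulation at low settings and raises it over days.
- Seizures, under the management of complications, reasons that kindled seizures are unlikely because the chosen parameters will not induce after-discharges.
- Prior findings with amygdala neurosurgery in humans describes one case at 130 Hz, 120 μsec and 2 to 6.5 V as close to the settings planned here.
- Deep brain stimulation, in the background, states that "amplitude determines the strength of the effect, and frequency determines activation or inhibition".

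**The concern.** The telemetry session exists to try stimulation settings under live EEG before patients go home on them. A back-off rule serves that purpose if the setting it leads to was observed in the session, or is clearly a smaller exposure than one that was. For amplitude this is plausible, since the document treats amplitude as the strength of the effect.

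Frequency differs in two ways. The tested range is narrow, so a 60% limit may not fall inside it. And the document describes frequency as governing the kind of effect, not its strength, so a lower frequency is not self-evidently a weaker dose.

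At stake is whether a subject with an after-discharge at the last step continues long-term on a combination that the session never examined, while the seizure section assures the reader that after-discharges will be avoided. Seizure is one of the two risk categories the protocol calls most serious for neuromodulation.

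**Working it through.** **Inputs**, all from the telemetry section unless stated:
- Limit = 0.60 × threshold, applied to the last parameter changed.
- Amplitude: start 2.5 V, maximum 7 V.
- Pulse width: start 120 μsec, maximum 210 μsec.
- Frequency: start 160 Hz, maximum 200 Hz.
- Comparison case (Prior findings): 130 Hz.

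**Reproducing the protocol's example.** 0.60 × 5 V = 3.0 V, which matches the stated limit.

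**Frequency step.** 160 Hz was already in use during the two earlier steps, so an event attributed to frequency has a threshold above 160 and at most 200 Hz.
- Lower end: 0.60 × 160 = 96 Hz (not itself reached).
- Upper end: 0.60 × 200 = 120 Hz.
- Threshold needed for the limit to reach the 160 Hz start: 160 / 0.60 = 266.7 Hz, above the 200 Hz maximum.
- Threshold needed for the limit to reach 130 Hz: 130 / 0.60 = 216.7 Hz, also above the maximum.

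So no possible frequency-step event gives a limit inside the tested range or as high as 130 Hz. The rule even excludes 160 Hz, which such a subject has just tolerated through both earlier steps.

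**The other two steps, for contrast.**
- Amplitude: 0.60 × 2.5 = 1.5 V to 0.60 × 7 = 4.2 V. The limit is inside the tested range when the threshold is at least 2.5 / 0.60 = 4.17 V.
- Pulse width: 0.60 × 120 = 72 μsec to 0.60 × 210 = 126 μsec. The limit is inside the tested range when the threshold is at least 120 / 0.60 = 200 μsec.

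For these steps the limit can fall inside the tested range. For frequency it cannot.

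**Where the other parameters stand.** By the frequency step, amplitude and pulse width may be at 7 V and 210 μsec. A bar on increases has two readings:
- Measured from the telemetry values, it requires no reduction from 7 V and 210 μsec.
- Measured from the low settings at which long-term stimulation starts, it holds them low.

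The text does not choose.

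**Does the charge-density limit settle it?** The documents give neither contact area nor impedance. Assume a contact area of 0.06 cm². Charge density = (V / impedance) × pulse width / area. At 7 V and 210 μsec:
- 500 ohm: 49.0 μC/cm²
- 750 ohm: 32.7
- 1000 ohm: 24.5
- 1500 ohm: 16.3

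The limit of 30 is met at 7 × 210 / (0.06 × 30) = 817 ohm. On this assumption it blocks the combination below about 817 ohm and allows it above.

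**The case against.** The strongest reply is that the rule sets a ceiling. A ceiling below a test session's starting value contradicts nothing, because no minimum long-term setting is stated and stimulation starts low anyway. For amplitude and pulse width this stands: a reader might infer that limits below 2.5 V or 120 μsec conflict with the protocol, but they do not. For frequency it answers only the charge of logical contradiction. The ceiling still leaves nothing but frequencies outside the session's range.

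Several stronger readings are tempting and should not be drawn.
- **That this is the protocol's only limit on stimulation.** It is not. There is the charge-density limit, reversal of settings after sustained side effects, slow escalation, 30 minutes of observation after each adjustment, and monthly EEGs with removal from the study for epileptiform discharges. The charge-density limit, however, is given to prevent tissue damage, and the EEGs detect a problem after exposure.
- **That the programming sequence flatly contradicts the rule.** The worked example can be read as making the telemetry limit qualify that sequence, and the sequence's last step is a change in frequency, not necessarily an increase. What remains is that the sequence does not say it is subject to the limit.
- **That a subject with a late event is treated more leniently than the one in the 5 V example.** These are different subjects with different demonstrated tolerance, so comparing their settings shows nothing.
- **That the limit moves patients toward seizure-provoking stimulation.** The background says of earlier depth-electrode work that "These settings were meant to generate seizures or other symptoms that would be related to the amygdala", but that was 5 to 10 Hz combined with high current and charge density. It does not carry over to 96 to 120 Hz. The same paragraph puts the planned frequency at 20 to 30 times 5 to 10 Hz, that is 100 to 300 Hz, so the document does not show that 100 to 120 Hz is outside high-frequency stimulation.

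Two further qualifications stand. Untested means untested at telemetry, because the intraoperative test states no frequency. And a fuller protocol or programming manual may treat the frequency step separately. But this is a rule stated with its numbers, and the difficulty follows from those numbers, not from missing detail.

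**Conclusion.** The point holds for the frequency step. Every possible event there gives a long-term ceiling above 96 and up to 120 Hz, outside the 160 to 200 Hz tested at telemetry and below the 130 Hz case cited as close to the plan. That is arithmetic on stated values and rests on no assumption.

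That amplitude and pulse width could remain at 7 V and 210 μsec is one of two readings of an unanchored clause. Whether the charge-density limit would prevent it depends on impedance and contact area, which are not given.

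As written, the rule is at odds with the session's purpose and weakens the assurance in the seizure section. The document does not show that cutting frequency proportionally lowers risk. It does not show that it raises risk either, and that judgement is clinical. How many of the six subjects would be affected cannot be estimated, since no event rate is given.

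**What to change.** The telemetry, programming, neuromodulation risk-reduction and seizure sections, together with the comparison case in the background, must be reconciled. The investigators and the DSMB should:
- restate the back-off rule for an event at the frequency step so that it fits the range tested under EEG;
- state the level from which the other parameters may not be increased;
- make the programming sequence expressly subject to the telemetry limits.

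Which limits are right is for them to decide; no setting or rule is proposed here. The cost is one amended paragraph with IRB and DSMB notification.

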## Methods/Design

### Purpose and justification of the study

The purpose of the current study is to evaluate the safety and potential therapeutic benefit of the Medtronic Activa DBS system implanted bilaterally in the BLn of the amygdalae in combat veterans with severe, chronic, treatment-resistant PTSD. DBS is considered a safe, nondestructive, and reversible therapy for neurological and psychiatric conditions. Despite being safe, DBS carries risks related to the surgery as well as risks associated with the neuromodulation. We expect the rate of complications from the amygdala BLn implantation procedure to be comparable to reported risks in other DBS applications, as reviewed elsewhere[147] and as detailed below.

Characterizing potentially undesirable effects of chronic high-frequency DBS of the amygdala is a principal aim of the study. While we expect there to be a low risk of serious adverse effects, the study involves extensive monitoring for psychiatric, neurologic, and neuropsychological adverse effects as described below and listed in Additional file1.

The duration of the investigation will be 24 months for each subject following device implantation and randomization. The subjects will be followed biannually once they exit the protocol. The presence of a significant other engaged in the healthcare of the patient will assist in early detection of adverse effects, as well as evaluating functional benefits.

We believe the risks involved, and the burden of extensive repeated assessments, are justified because treatment-resistant PTSD is a very serious illness associated with significant suffering and morbidity. There are currently no good treatment options for patients who have failed to improve with psychotherapy and several lines of psychopharmacological agents. We believe that BLn DBS is a therapeutic option worth investigating.

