
Study assessments will occur weekly for five months after implantation, monthly for ten months, then every three months for the final nine months. All study measures will be completed at baseline, and then repeated as follows (see Additional files1,2,3 and4 for detailed descriptions, and Additional file5 for overall study timeline):Clinical monitoring and system status check at each visit.Stimulator adjustments, CAPS, MADRS, YMRS, C-SSRS, LFIPS, ADIPS, CGI, vital signs, and EEG monthly for 15 months, then every three months for nine months.GAF, SF-36 V, DTS, HAMA, ECG every three monthsNeuropsychological test battery at 6, 12, and 24 monthsResting and trauma script provoked PET Scan at 15 months

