
### Management of potential complications and therapy cessation

#### Seizures

Because the stimulation parameters chosen in this study will avoid the induction of afterdischarges, it is unlikely that kindled seizures will occur. However, given the possible kindling effect of chronic DBS of the amygdalae, monthly EEG studies will be performed to detect epileptiform discharges before epilepsy would be fully established. Subjects with confirmed epileptiform discharges, such as sharp waves, spike and slow waves, polyspikes, or a full seizure will not be kept in the study. The EEG will be interpreted by a board-certified clinical epileptologist (JC).

Any patients who suffer from a seizure will follow up with our epileptologist on a monthly basis for a period of six months, and then every three months for the duration of the trial. Following the completion of the trial, the patient will continue to be followed up as clinically indicated.

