### Therapy cessation

The decision to stop the stimulation unilaterally (one electrode) or bilaterally (both electrodes) will be made on a case-by-case basis and the IRB will be informed. The decision to stop the stimulation is not necessarily irreversible and could be used in certain cases to confirm that a specific symptom is not caused by the stimulation. Patients who stop the stimulation, but agree to follow-up, will be seen at the same frequency, following the protocol. As a general guideline, cases where the stimulation would be stopped include:After being fully informed, the patient wishes to stop the stimulation.The patient is suffering from a deterioration of his psychological condition thought to be related to the stimulation. He has been unresponsive to changes in DBS parameters.The stimulation is causing intolerable side effects unresponsive to changes in DBS parameters.The patient has suffered from a seizure as a result of DBS.The patient has to undergo treatment for a life-threatening condition and stimulation may interfere with the treatment.The patient has become seriously non-compliant with the course of therapy (for example, missing several appointments, engaging in behavior that places him or others at risk related to the device, or serious substance-use disorder).

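### Subjects with confirmed new epileptiform discharges or a seizure are removed from the study, which ends their scheduled safety assessments and conflicts with the Therapy cessation rule for a DBS-caused seizure

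*Protocol article*

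**What the plan says.** Three sections of the protocol article say what happens when stimulation appears to have provoked epileptic activity.

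- **Electroencephalogram telemetry session and deep brain stimulation initiation**, on the monthly EEGs: "Subjects with newly developed epileptiform discharges will be terminated from the study and managed clinically". The same section treats an after-discharge at the initial telemetry session differently: that subject stays in the study at reduced settings.
- **Seizures**: the list of confirmed discharge types ends "polyspikes, or a full seizure will not be kept in the study". The section then adds: "Any patients who suffer from a seizure will follow up with our epileptologist on a monthly basis for a period of six months", followed by three-monthly visits until the trial ends.
- **Therapy cessation**: among the cases in which stimulation would be stopped, as a general guideline, is "The patient has suffered from a seizure as a result of DBS". The consequence is not exit: "Patients who stop the stimulation, but agree to follow-up, will be seen at the same frequency, following the protocol". Stopping is decided case by case: "The decision to stop the stimulation is not necessarily irreversible".

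Two other places bear on this. Outcome measures sets the schedule: "CAPS, MADRS, YMRS, C-SSRS, LFIPS, ADIPS, CGI, vital signs, and EEG monthly for 15 months, then every three months for nine months", with the neuropsychological battery at 6, 12 and 24 months. Purpose and justification of the study says of later contact: "The subjects will be followed biannually once they exit the protocol".

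**The concern.** Stopping stimulation protects the subject. Leaving the study does not, but the telemetry and Seizures sections tie the two together. The Therapy cessation section separates them for other stimulation harms, such as psychological deterioration or intolerable side effects, and also for a seizure caused by DBS. One event therefore has two dispositions.

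Study aims makes safety the primary aim and lists EEG change over time under it. Design of the study justifies the two-year period partly by the chance that adverse effects accumulate or alter. Data analysis compares the scales with baseline chiefly as a safety check. The open question after a discharge or seizure is whether EEG, mood, behaviour and cognition recover once stimulation is off. The removal rule ends scheduled collection of that information in the subjects who could supply it. Individual results are to be published, so a removal would be visible, but assessments never made cannot be reported.

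**Working it through.** **1. The rules side by side**

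| Event | Telemetry section | Seizures section | Therapy cessation section |
|---|---|---|---|
| After-discharge at telemetry session | Stays in study, reduced settings | Not addressed | Not addressed |
| New confirmed discharges, no seizure | Removed from study | Removed from study | Not listed |
| Seizure caused by DBS | Not addressed | Removed from study; epileptologist visits | Stimulation stopped; protocol visits continue if the patient agrees |

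The last row is a contradiction. The middle row is consistent, and there the issue is the design choice itself.

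**2. Scheduled assessments lost**

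Inputs, from Outcome measures: CAPS and EEG monthly to month 15, then every three months for nine months (months 18, 21, 24).

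Total = 15 + 3 = 18 post-implantation CAPS and EEG assessments. These are assessments, not clinic visits; clinic visits are weekly for the first five months.

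Lost after removal following the month *m* visit (*m* ≤ 15) = 18 − *m*.

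- *m* = 3: 18 − 3 = 15, and 15/18 = 83%. Neuropsychological batteries lost: 3 of 3.
- *m* = 6: 18 − 6 = 12, and 12/18 = 67%. Batteries lost: 2 of 3 (months 12 and 24).

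The 12-month CAPS, which Data analysis names as the primary outcome measure, is lost only if removal comes before that visit. Months 3 and 6 are illustrations; the article gives no event risk, so no probability is attached.

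**3. Follow-up that remains**

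*After a seizure*, epileptologist visits monthly for six months and then every three months, counted to month 24:

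- Seizure at month 3: months 4–9 (6) plus months 12, 15, 18, 21, 24 (5) = 11.
- Seizure at month 6: months 7–12 (6) plus months 15, 18, 21, 24 (4) = 10.

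No study scales are named for these visits.

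*After discharges without a seizure*, there is clinical management, and possibly the biannual follow-up. Assuming that it covers removed subjects and means every six months from exit:

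- Exit at month 3: months 9, 15, 21 = 3 contacts.
- Exit at month 6: months 12, 18, 24 = 3 contacts.

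Again, no assessments are named.

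**4. Scale**

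With six subjects, one removal is 1/6 = 17% of the sample.

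**The case against.** Read together, the sections suggest that the sponsor means to keep watching these patients. The Seizures section schedules epileptologist visits to the end of the trial immediately after the removal sentence, and the Therapy cessation section keeps consenting patients on protocol visits. That removal ends the scheduled battery is inferred from the wording, not stated. The event itself is recorded as an adverse event. The trigger is narrow, and the article condenses a fuller protocol that may say what is assessed after termination.

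Much of this stands, and it limits the point. A reader might infer that safety follow-up stops altogether. The documents do not support that: contact continues after a seizure, and may continue after discharges. A reader might infer that any provoked discharge ends participation, but subjects with after-discharges at the telemetry session are explicitly kept. Nor is there a biased treatment test to correct, because Data analysis says no formal treatment hypothesis is tested.

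The objection does not remove the conflict. Calling the Therapy cessation list a general guideline does not help: if the Seizures section prevails as the more specific rule, the result is removal. For discharges without a seizure, removal is the only explicit rule. These are rules that the article states, not details that it omits, and none of the remaining contacts is said to include the scheduled EEG, C-SSRS, ADIPS, CAPS or neuropsychological tests.

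**Conclusion.** The point holds in this limited form. For a DBS-caused seizure, the article gives two incompatible dispositions. For new confirmed discharges without a seizure, it consistently prescribes removal. On the natural reading of removal, 15 of 18 scheduled CAPS and EEG assessments are lost after a month 3 exit and 12 of 18 after a month 6 exit, together with any 12-month CAPS not yet done. The loss is of safety information in a trial whose primary aim is safety.

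It is partly offset after a seizure by about 11 or 10 epileptologist contacts. It is barely offset after discharges alone, where perhaps three contacts remain under the assumption stated above. The conclusion rests on reading removal from the study as the end of the study schedule, on the illustrative exit months, and on the subject's willingness to continue.

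**What to change.** In the telemetry and Seizures sections, replace removal from the study with stopping study stimulation and managing the subject clinically. Then apply the existing Therapy cessation rule to both events, so that consenting subjects continue the scheduled safety and CAPS assessments to month 24 off stimulation.

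A permanent ban on restarting stimulation is not needed for this. Any restart decision can stay with the clinical and safety oversight already in place. Nor does the change require a new analysis rule for the 12-month CAPS.

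The cost is a wording change in two sections; the assessments are already on the schedule. The real downside is continued visit burden, which the Discussion names as the study's principal limitation and which a subject may decline.
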